## Abstract

Excessive consumption is on the rise, as is apparent in growing financial debt and global greenhouse gas emissions. Voluntary simplicity, a lifestyle choice of reduced consumption and sustainable consumer behavior, provides a potential solution for excessive consumers. However, voluntary simplicity is unpopular, difficult to adopt, and under researched. The outlined research project will test a method of promoting voluntary simplicity via user-generated content, thus mimicking an existing social media trend (Minimalism) in an empirical research design. The project will test (a) whether the Minimalism trend could benefit consumers interested in reducing their consumption, and (b) whether self-transcendence (i.e., biospheric) and self-enhancement (i.e., egoistic and hedonic) values and goals have a similar impact in promoting voluntary simplicity. A one-week intervention program will test the efficacy of watching user-generated voluntary simplicity videos in reducing non-essential consumption. Each of the two intervention conditions will present participants with similar tutorial videos on consumption reduction (e.g., decluttering, donating), while priming the relevant values and goals (self-transcendence or self-enhancement). These interventions will be compared to a control condition, involving no user-generated content. Participants will undergo baseline and post-intervention evaluations of: voluntary simplicity attitudes and behaviors, buying and shopping behaviors, values and goals in reducing consumption, and life satisfaction. Experience sampling will monitor affective state during the intervention. We provide a detailed stepwise procedure, materials, and equipment necessary for executing this intervention. The outlined research design is expected to contribute to the limited literature on voluntary simplicity, online behavioral change interventions, and the use of social marketing principles in consumer interventions.

## Excessive consumption

Consumption becomes excessive when it exhausts the consumer's financial or mental resources, or when it creates extreme environmental consequences, thus negatively affecting individual and societal well-being (Sheth et al., 2011). During the last decade, US consumption has risen dramatically; in 2007, consumption accounted for 72% of the American GDP. One factor which may contribute to excessive consumption is Materialism. Materialistic individuals consider material goods as an important part of their identity (Belk, 1984). They perceive material possessions as central to their status and happiness (Richins and Dawson, 1992). In a recent meta-analysis examining materialism and personal well-being, a significant negative relationship was found between the two (Dittmar et al., 2014). In an effort to reduce excessive consumption and increase consumer well-being, this project proposes a method to engage consumers in a reduced consumption lifestyle, namely, voluntary simplicity.

## Voluntary simplicity

A frequently proposed solution to excessive consumption and its negative affects is voluntary simplicity (Etzioni, 1998; Alexander and Ussher, 2012); the consumer movement of adopting a simplistic lifestyle. Voluntary simplicity involves a consumer's independent decision to reduce and replace non-essential products and services with non-material life elements, in an attempt to increase life satisfaction and meaning (Etzioni, 1998; Huneke, 2005). Non-essential items and services can be defined as things that are irrelevant for the achievement of one's life purpose (McGouran and Prothero, 2016). For example, voluntary simplicity behaviors include: composting, recycling, decluttering (Huneke, 2005), self-sufficiency and use of pro-environmental transportation (Alexander and Ussher, 2012). While this lifestyle is promising in its potential to reduce consumption and increase well-being, is it difficult to adopt (McGouran and Prothero, 2016).

### Minimalism

The scholarly concept of voluntary simplicity has recently been adapted into popular culture, under the term *Minimalism*. Minimalism often encompasses user-generated content, such as videos, texts, and images that promote consumption reduction. Minimalism content is largely shared via YouTube, Facebook, Twitter and similar online social networking services. Additionally, there are numerous blogs, online forums and websites devoted to Minimalism^1^. In these online sources, viewers can find information about Minimalism, tips on how to adopt this lifestyle, tutorials, and personal narratives of successful minimalists.

The Minimalism phenomenon, to a lesser degree than voluntary simplicity, seems to utilize an aesthetic approach. Minimalism can be studied as an aesthetically pleasing trend, relating to both fashion and web design. For example, narratives of fashion bloggers dedicated to a Minimalistic style revealed a strong emphasis on simplicity, elegance, sophistication and cleanliness, which were achieved in particular by choice of coloring and scarce use of patterns (Karg, 2015). It is yet early to determine whether the Minimalism phenomenon is a passing trend or a new wave of conscious consumerism, but Minimalism may have the power to engage consumers in sustainable behaviors.

## Self-transcendence and self-enhancement values and goals

One way through which consumer interventions could reduce materialism and promote sustainable consumption, is through the activation of relevant values and goals (Kasser, 2016). In other words, Minimalism videos may not only serve the purpose of directly increasing voluntary simplicity behaviors through tutorials; these videos are also a channel through which relevant ecological values could be activated and strengthened. Thus, user-generated content on Minimalism could promote personal norms of sustainable consumption, creating longer-term impact on consumer behavior.

Previous research has consistently shown that a biospheric value orientation is positively associated with ecological attitudes and beliefs, and is thus conducive to sustainable behavior (e.g., Stern, 2000; de Groot and Steg, 2008). A biospheric value orientation is a type of self-transcendence value, which emphasizes the environment and the biosphere over one's own personal benefit (Stern et al., 1993).

Self-enhancement values, on the other hand, promote one's own benefit over that of others or the environment, e.g., egoistic and hedonic values (Schwartz, 1992). Egoistic and hedonic values are negatively associated with ecological attitudes and sustainable behaviors (Steg et al., 2014). Moreover, these values are closely clustered with materialism, and thus could promote excessive consumption (Burroughs and Rindfleisch, 2002; Kasser, 2016).

### Self-transcendence and self-enhancement in minimalism videos

Although, previous literature suggests that self-enhancement values have a negative impact on sustainable behavior, user-generated content on Minimalism seems to be focused exactly on these values. Exploratory research of the Minimalism phenomenon found that engagement in Minimalism is associated with a personal goal to reduce stress (hedonism) and save money (egoism), but not with environmental concern ([name], unpublished manuscript). Thus, we argue that self-enhancement goals might be utilized to promote sustainable consumer behavior. However, it remains unclear whether self-enhancement goals could be as effective as self-transcendence goals in promoting sustainable behavior.

## Objectives

The project will test whether user-generated content promoting either self-transcendence or self-enhancement values and goals could be effective in reducing excessive consumption, as well as increasing well-being. The effectiveness of the interventions will be tested by measuring their effects on life-satisfaction, intent to adopt voluntary simplicity, and purchasing intent and behavior. The project's main research questions are:
Could user-generated content promoting voluntary simplicity reduce excessive consumption?Are self-enhancement goals as effective in promoting sustainable behavior as self-transcendence goals, in user-generated Minimalism content?

We are also interested in whether exposure to user-generated content promoting voluntary simplicity affects one's well-being. Finally, the relationship between one's intent to reduce consumption and one's consumption behavior might generate meaningful insights.

## Design

A weeklong intervention program will test the efficacy of watching voluntary simplicity videos in reducing non-essential consumption. The first condition will promote voluntary simplicity while priming self-transcendence values and goals, and the second condition will promote voluntary simplicity while priming self-enhancement values and goals. These two interventions will be compared with a control condition which only measures participant's affective state during the intervention week. All participants will undergo baseline and post-intervention evaluations of values and goals in consumption reduction, voluntary simplicity attitudes and behaviors, spending behaviors, and life satisfaction directly before and directly following the intervention, respectively. A one-month follow up measurement will also be taken. The difference between measurements before and after the intervention will serve as our dependent variables.

## Intervention

A key component in this study is the video stimuli employed. Videos have proven to be more effective and persuasive than other modalities of communication (Mohammadi et al., 2013). To maintain a high level of reliability and validity, the research team will create the intervention videos in-house. To create valid video stimuli several measures will be taken:

### Video checklists

Video checklists describe the key concepts and behaviors to be addressed in the video stimuli. These checklists detail the following stimuli requirements, per condition:
Content: information conveyed (stable across intervention conditions)Condition priming: what values and goals will be primed in the opening and closing statements of the videos, as well as the visual stimuli (self-transcendence vs. self-enhancement)Style: the presenter's tone and expression (stable across intervention conditions).

Due to internal reliability concerns, one presenter will appear in all videos, for both intervention conditions. The presenter will be a female in her twenties, similarly to many Minimalism vloggers. Appendix A presents an example of a video checklist.

The research team will contact several social and consumer psychologists to review these checklists and approve that they (a) prime self-transcendence and self-enhancement values and goals, per condition, and (b) promote consumption reduction, prior to video creation.

### Video pre-testing

The videos will be pretested in a convenience sample of international psychology students at the advanced undergraduate and graduate level. We aim to test the face validity of the videos. Thus, the pre-test population will consist of young consumers with a basic scientific knowledge on motivation, values, and goals. The pre-test sample will therefore be slightly different from the population addressed in the main study. Participants will watch subsets of videos from both intervention conditions and rate the face validity of the videos (e.g., “Did the presenter promote biospheric values?”, “Did the presenter promote egoistic values?”). They will also note any manipulation concerns or potential confounds in the video stimuli of both conditions. Additionally, participants will rate how entertained, focused and interested they were when watching the videos. The latter measures will be used to estimate main-study participants' motivation in watching the daily video stimuli during the weeklong intervention. If a video receives a low score on either validity or entertainment value during the pre-test, the research team will revise the videos based on pre-test comments, and re-test them on a similar sample.

### Mobile application

A mobile application will be developed and used in the study for stimuli presentation, data collection, communication, and once the study is complete, a personalized progress report. Video stimuli will be embedded into Qualtrics questionnaires, which will be linked in the mobile application. This will allow participants to easily fill-out the questionnaires before and after viewing the video stimuli. Time spent viewing the videos will be recorded by a “timing” function in Qualtrics.

The mobile application push-notification system will remind participants to view the video and fill in a questionnaire on a daily basis throughout the weeklong intervention. Thus, participants will receive one push-notification a day, until the intervention is complete. The mobile application will also allow both the participants and research team to communicate via email. This will be useful if any problems or questions arise. Finally, users of the mobile application will receive a personalized progress report once the study is completed.

## Procedure

At baseline, all participants will download a free mobile application. Participants will complete an intake survey on Qualtrics, through a link in the mobile application. Following intake, participants will be randomly allocated to one of the three experimental conditions, and complete a battery of questionnaires measuring dependent and independent variables (see t0 in Figure 1). After baseline measurements, the intervention will commence. In the two intervention conditions, participants will watch one video daily for 6 days. Both intervention and control condition participants will complete a daily mood measurement (see t1 through t6 in Figure 1). On the last day of the intervention, participants will complete questionnaires measuring the dependent and independent variables a second time (see t7 in Figure 1). One month after intervention completion, the dependent variables will be measured again (see t_end_ in Figure 1).

**Figure 1 F1:**
[figure not shown]
Study outline. ^*^t+1 equals one day; t0−t7 are completed within one week. ^**^t_end_ will take place one month after intervention completion (t7).

## Methods

### Ethics process

Due to the study's intervention design, careful consideration was put into ethical procedures executed by the research team. Ethical approval has been granted for this study. In addition to standard procedures, such as voluntary participation and dropout, several processes are in place to reduce potential harm to participants' well-being.

Firstly, participants who struggle with compulsive buying, hoarding, or other addictive behaviors are regarded as sensitive populations, and will be asked through a consent form not to take part in the study. Individuals diagnosed with Compulsive Buying Disorder (CBD) repeatedly engage in excessive spending behaviors and cognitions due to irrepressible impulses, which result in anxiety or impairment (Black, 2007). CBD diagnosed individuals will be ineligible to participate in the study because of two main reasons; (a) the topic and nature of the study could potentially cause harm or distress to the individual and (b) the study's purpose, to explore potential solutions to reduce excessive consumption, will be directed toward the general population of consumers and not those suffering from a clinical buying disorder. Thus, an in-take survey will employ a validated self-report clinical screener for CBD (Faber and O'Guinn, 1992). Participants scoring over the clinical threshold will be excluded from the study; they will be notified of their ineligibility, via email, within two days of their in-take questionnaire submission. They will also be sent additional information on professional help networks for compulsive buyers^2^. A diagnosis will not be provided to participants due to the research team's lack of clinical training and the absence of differential diagnosis.

Similarly, participants will be asked to report any undesirable changes in mood and behavior during the intervention by contacting the research team. Participants reporting an increase in buying behavior or severe decline in well-being, will be interviewed by e-mail, and dismissed from the study. Full reporting of these instances, should there be any, will be included in the results section of disseminated work emerging from this project.

After the intervention is completed, including a one-month follow-up, the research team will conduct initial analysis on the effectiveness of the employed interventions. Specifically, conducted analysis will test whether either one or two of the employed interventions prove to be beneficial in reducing excessive consumption and increasing well-being, in comparison to the control condition. If one or both interventions prove to be effective, they will be offered to participants who did not experience them while participating in the study. Thus, all participants will be afforded the opportunity to take part in an effective intervention for consumption reduction, should the research team identify one. Participants will also receive debriefing of the study and will be exposed to all three conditions employed in the study design.

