#### Intake screeners

##### Assessment of Compulsive Buying Behavior

The Clinical Screener (CBCS; Faber and O'Guinn, 1992) is one of the most validated and replicable self-report scales measuring compulsive buying behavior, having been found to correctly classify 88% of compulsive buyers (Faber and O'Guinn, 1992). The CBCS contains seven statements that respondents are required to rate their agreement with (1 = Strongly disagree to 5 = Strongly agree) (e.g., “If I have any money left at the end of the pay period, I just have to spend it”) or their frequency of experiencing given behaviors/feelings (1 = very often to 5 = never) (e.g., “Bought things even though I could not afford them”) on five-point Likert scales. A total score is calculated, and a threshold measurement determines whether an individual is considered a compulsive buyer.

Faber and O'Guinn's (1992) compulsive buying scale has, however, been criticized for only addressing the impulse control dimension of compulsive buying behavior and not the obsessive-compulsive dimension, as well as not being accommodating to buyers that have higher incomes (Ridgway et al., 2008). To compensate for these limitations, the Compulsive-Buying Index (CBI) developed by Ridgway et al. (2008) will be used in addition to the CBCS, thus presenting a more comprehensive measurement of compulsive buying behavior.

The Compulsive-Buying Index (CBI) is a well-validated measure of compulsive buying behavior (Ridgway et al., 2008). The CBI contains six items measuring two dimensions of compulsive buying; three items for obsessive-compulsive buying (e.g., “My closet has unopened shopping bags in it”) and three items for impulsive buying (e.g., “I buy things I don't need”). Responses are given on a seven-point Likert scale either indicating agreement with statements (1 = strongly disagree to 7 = strongly agree) or frequency of experiencing given behaviors/feelings (1 = never to 7 = very often). A total score is calculated, and a threshold measurement determines whether an individual is considered a compulsive buyer.

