#### Post-intervention questionnaire

The effectiveness of the intervention will be measured by the difference of participants' pre- and post-intervention measurements, controlling for covariates. Therefore, all intake questionnaires will be repeated in the post-intervention phase. Along with these repeated scales, several additional measures will be administered.

Two additional questions will measure participants' attitude toward the videos. The first item will measure whether participants would recommend the video to friends with a similar goal (i.e., “Would you recommend these videos to a friend who also wanted to reduce their non-essential consumption?”). The second item will measure participants' intention to continue watching similar videos online (i.e., “Would you watch similar videos online?”). Participants would be required to indicate their answer on a nine-point scale (0 = not at all to 8 = definitely) for both questions. Lastly, an open-ended question will allow participants to share what they thought was interesting, difficult, or helpful during the one week of intervention.

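### The individual harm report is built from cases participants bring forward, with no prompted question stated at t7 or t_end, and no response is stated for a new over-threshold compulsive-buying score on the repeat screen

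*Protocol article*

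**What the plan says.** The harm provisions are in the protocol article, Ethics process. The route for harm cases is that "participants will be asked to report any undesirable changes in mood and behavior during the intervention by contacting the research team". Those who report more buying or a severe drop in well-being are interviewed by e-mail and leave the study. The article then promises: "Full reporting of these instances, should there be any, will be included in the results section of disseminated work".

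The same section excludes people over the threshold of the clinical screener for compulsive buying (CBCS), partly because "the topic and nature of the study could potentially cause harm or distress to the individual". They are told within two days of the intake questionnaire. On support it says: "They will also be sent additional information on professional help networks for compulsive buyers".

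Three other places bear on this:

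- **Procedure:** mood is measured daily from t1 to t6 in all three conditions, and the questionnaires are given again at t7. "One month after intervention completion, the dependent variables will be measured again".
- **Assessment of Compulsive Buying Behavior:** the CBCS is listed among the intake screeners and described as "having been found to correctly classify 88% of compulsive buyers". A second thresholded scale, the CBI, is added to make up for its limitations.
- **Post-intervention questionnaire:** "all intake questionnaires will be repeated in the post-intervention phase". In addition, "an open-ended question will allow participants to share what they thought was interesting, difficult, or helpful during the one week of intervention".

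**The concern.** There are two linked points.

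First, the harm report is defined by who writes in. Worsening that a participant does not volunteer has no stated way into it, even though every participant is surveyed again at t7 and one month later. The request is also worded for the intervention period, while measurement runs on to t_end. A reader of the results could not tell a low count of harms from a low rate of reporting.

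Second, the team will hold a second compulsive-buying score for each person who completes t7. At intake it treats an over-threshold score as reason to send help information. For the same score at t7 the article states no response.

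What is at stake is how complete the safety account is, and a small measure of participant protection. The article itself regards compulsive buyers as a group the study could harm. It also recruits people who find it difficult to cut their non-essential consumption (Participant criteria), so some who enrol may be near the threshold.

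**Working it through.** **Text check.** The first point is a matter of wording, and the article gives no figure to reproduce.

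| Question | What the article states | Where |
|---|---|---|
| How do individual harm cases reach the team? | Participants contact the team | Ethics process |
| What period does the request name? | The intervention | Ethics process |
| What is fully reported? | The cases so raised | Ethics process |
| Which systematic data could show harm? | Daily affect t1–t6, life satisfaction, buying, in all arms | Procedure; Measures |
| Are those data linked to the individual harm report? | Not stated | – |
| Is there a prompted question on undesirable change at t7 or t_end? | Not stated; the t7 open question asks for something else | Post-intervention questionnaire |
| When does an over-threshold screen lead to help information? | At intake | Ethics process |
| Is the screen repeated? | Yes, on the plain wording that covers every intake questionnaire | Post-intervention questionnaire |
| What response follows a new over-threshold repeat score? | Not stated | – |

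**Compulsive buyers who could pass the intake CBCS.** Inputs: correct classification of compulsive buyers 0.88 (Assessment of Compulsive Buying Behavior); 250 recruited (Sample size), taken here as the number enrolled. Assumed: prevalence p among those screened, specificity 1, and the CBCS as the only filter.

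Share of enrolled = 0.12p / (1 − 0.88p)

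- p = 0.05: 0.006 / 0.956 = 0.0063; × 250 = 1.6
- p = 0.10: 0.012 / 0.912 = 0.0132; × 250 = 3.3
- p = 0.20: 0.024 / 0.824 = 0.0291; × 250 = 7.3

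With an assumed specificity of 0.85, the share is 0.12p / (0.12p + 0.85(1 − p)), giving 1.8, 3.9 and 8.5.

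**New threshold crossings by chance at t7.** Assume that intake and repeat scores are bivariate normal with retest correlation r and no true change, and that a fraction p exceeds the cut-off c at intake. Those over c are excluded, so the quantity needed is

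P(X2 > c | X1 ≤ c) = [(1 − p) − P(X1 ≤ c, X2 ≤ c)] / (1 − p)

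| p (assumed) | r = 0.9 | r = 0.8 | r = 0.7 |
|---|---|---|---|
| 0.05 | 0.019 | 0.027 | 0.032 |
| 0.10 | 0.035 | 0.049 | 0.059 |
| 0.20 | 0.063 | 0.089 | 0.109 |

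The range 0.019 to 0.109 gives 3.8 to 21.6 of 198 completers (the required N under Sample size). With 198 / 3 = 66 per arm, it gives 1.3 to 7.2 per arm. Both p and r are assumptions.

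**The case against.** The strongest objection is that this is silence and not error: a journal article may leave safety follow-up to the full protocol or the ethics file, and the study has ethics approval. That stands for part of the second point. A reader might infer that a participant newly over the threshold at t7 would be sent nothing. The article does not say so; it only states no response. For the first point the objection is weaker, because the article sets a rule: cases come by contacting the team, and those are the cases reported.

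Next, undesirable change is measured in everyone. Daily negative affect, life satisfaction and buying are collected in the control condition too, and the open question asks what was difficult. This stands, and it limits the point to the individual harm report. A reader might infer that harm would go unseen; at group level that is not supported. The phrase about participants reporting more buying could be stretched to cover questionnaire answers, but the sentence before it describes reporting as contacting the team.

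Third, a reader might take the 88% to mean that 12 in 100 compulsive buyers enter the trial. The documents do not support that. People who struggle with compulsive buying or addictions are asked at consent not to take part, participants attest to having no such diagnosis, and the CBI is a second screener. Whether the CBI also excludes is unclear, since Ethics process names only the clinical screener.

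Fourth, a reader might infer that harms after t7 are shut out. Ethics process elsewhere uses the word intervention so as to include the one-month follow-up, and no end date is stated for the app's e-mail link. The wording is ambiguous, and no loss of late reports is shown.

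Last, the repeat screen rests on one sentence and is clear only for t7, and many new crossings could be noise. Both stand.

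**Conclusion.** The point holds as a minor one. As written, the individual harm report consists of cases that participants raise themselves. The systematic data on mood, life satisfaction and buying are not linked to it, and no prompted question is stated at t7 or t_end. Help information is stated for an over-threshold screen at intake, and no response is stated for the repeat.

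The numbers are illustrations. The figures of 1.6, 3.3 or 7.3 missed compulsive buyers among 250 treat the CBCS as the sole filter, with assumed prevalence and perfect specificity. The consent exclusions would lower them, as would the CBI if it is used to exclude; imperfect specificity would raise them slightly. The 4 to 22 chance crossings among 198 rest on assumed threshold rates and retest correlations, and show why a count of crossings cannot serve as evidence of harm by itself. No efficacy estimate, sample size or error rate is affected. Confidence is medium, because the repeat screen rests on a single sentence and the full ethics file may cover later referral.

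**What to change.** 1. Word the request to report undesirable changes so that it runs explicitly to t_end.
2. Add one prompted item on undesirable change in buying or mood at t7 and t_end, in all three conditions.
3. Send the existing help-network information, without a diagnosis, to anyone over the CBCS threshold on the repeat screen.
4. Report by randomised condition, descriptively only: volunteered cases, prompted reports, and the number newly over the CBCS threshold at t7. No test against control is advised, because chance crossings are common and the comparison has little power.

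The cost is one item at two existing time points and one short table; the help information is already prepared for intake. The downside is that some help e-mails will be triggered by measurement noise and reach people who do not need them.

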### Participant outreach

#### Sample size

Two hundred and fifty English-speaking subjects will be recruited for this study globally, via online methods. The number of participants needed is based on an a priori power analysis using G^*^Power software (*F*-test, ANOVA: Repeated measures, within-between-interaction; 1− β = .80, α = .05, Cohen's f = .10), which revealed that the study would require a total sample size of *N* = 198 (Faul et al., 2007). An additional 52 participants have been added to this estimated sample size to account for an assumed 20% dropout rate.

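### Dismissing participants because buying rose or well-being fell leaves outcomes missing because they were unfavourable; within-arm change is biased toward improvement and the contrast with control in an unknown direction

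*Protocol article*

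**What the plan says.** Under Procedure, allocation precedes the intervention week: "Following intake, participants will be randomly allocated to one of the three experimental conditions". During that week, according to Ethics process, "participants will be asked to report any undesirable changes in mood and behavior during the intervention by contacting the research team". The consequence follows: "Participants reporting an increase in buying behavior or severe decline in well-being, will be interviewed by e-mail, and dismissed from the study". Any reported increase in buying is enough; for well-being the decline must be severe. The rule is not limited to the video arms. For these cases the article promises this: "Full reporting of these instances, should there be any, will be included in the results section". It does not say that they still complete t7 or the one-month follow-up, or that they stay in the analysis.

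The triggers are also what the interventions are judged on. Objectives describes effectiveness as tested by "measuring their effects on life-satisfaction, intent to adopt voluntary simplicity, and purchasing intent and behavior". Ethics process adds that, after follow-up, "conducted analysis will test whether either one or two of the employed interventions prove to be beneficial in reducing excessive consumption and increasing well-being", relative to control; that result decides which intervention is offered to other participants. Post-intervention questionnaire defines the effect as a change: "The effectiveness of the intervention will be measured by the difference of participants' pre- and post-intervention measurements, controlling for covariates". The Proposed analysis regresses the post-intervention value on condition and baseline, and expects a fall over time in all arms and a larger one in the video arms.

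Sample size has one allowance for losses: "An additional 52 participants have been added to this estimated sample size to account for an assumed 20% dropout rate".

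**The concern.** This is selection on the outcome after randomisation. A participant whose buying rises and who says so is removed before t7, so the planned regression has no outcome for that person. The remaining participants look better than the arm they came from. Three readings of the data are affected: the pre-post change in each arm, any harm in a video arm, and the randomised comparison with control. The dropout allowance protects the number of participants, not the comparability of those who remain. Methods that assume data are missing at random do not suit losses triggered by the outcome, and no analysis plan can recover values that were never collected.

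**Working it through.** **The plan's own figures.** From Sample size: N = 198 (f = 0.10, power 0.80, alpha 0.05), raised to 250 for 20% dropout. With three groups, three measurements and a within-person correlation of 0.5 (all assumed; the article does not state them), the noncentral F calculation gives N = 202, and power 0.79 at N = 198, so the figure is approximately reproduced. Dropout: 198/0.80 = 247.5, rounded up to 248, against 250. The point does not rest on these figures. The loss of numbers is also minor: dismissing 5% on top of the 20% dropout leaves 250 × 0.80 × 0.95 = 190, with power 0.77 under the same assumptions.

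**Inputs that must be assumed.** The article gives no dismissal rate, reporting rate or threshold. Let the change score d be normal with mean μ and SD σ (negative = improvement; σ = 1 unless stated). A share q of those with d > c report and are dismissed, with q = 0.10 to 0.50 and c = 0 or 1.

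**Formula.** With a = (c − μ)/σ and p = 1 − Φ(a):

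- share dismissed = q·p
- observed mean change = [μ − q(μ·p + σ·φ(a))]/(1 − q·p)

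Example: μ = 0, c = 0, q = 0.25 gives p = 0.5 and φ(0) = 0.399. Dismissed: 0.25 × 0.5 = 12.5%. Observed change: −0.25 × 0.399/0.875 = −0.114, although the true change is 0.

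**Results over the whole range (SD of the change score).**

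| Situation | True | Observed |
|---|---|---|
| Change within one arm, no true change | 0 | −0.025 to −0.266 |
| Contrast, no effect, equal reporting | 0 | 0.000 |
| Contrast, real benefit (video −0.3, control −0.1) | −0.20 | −0.198 to −0.173 |
| Contrast, real harm (video +0.2, control 0) | +0.20 | +0.200 to +0.169 |
| Contrast, equal means, video-arm SD 1.3 | 0 | −0.013 to −0.085 |
| Contrast, no effect, video reporting double control | 0 | −0.012 to −0.152 |
| Contrast, no effect, control reporting double video | 0 | +0.012 to +0.152 |

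Only the first row has a fixed sign at no effect. The contrast can be unbiased, too favourable, too weak or spuriously harmful.

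**Effect on the test.** Simulated analysis of covariance with no true effect: 132 video and 66 control participants, baseline-post correlation 0.6 (assumed), results in SDs of the outcome.

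| Who is dismissed | Video / control dismissed | Bias | Type I error |
|---|---|---|---|
| 10% of those who worsen, both arms | 5% / 5% | 0.00 | 5% |
| 20% of worsened in video, 10% in control | 10% / 5% | −0.03 | 6% |
| 10% of worsened in video, 20% in control | 5% / 10% | +0.03 to +0.04 | 5 to 6% |
| Exactly the largest increases | 10% / 5% | −0.07 | about 12 to 13% |
| Exactly the largest increases | 5% / 0% | −0.08 | about 12% |

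**Effect on the change over time.** If the largest 5% of increases go in every arm, the mean change shifts by φ(1.645)/0.95 × SD of change = 0.1086 × √(2(1 − 0.6)) = 0.1086 × 0.894 = 0.097 SD toward improvement. At N = 198 the standard error of a mean change is 0.894/√198 = 0.064, so this worst-case shift is about 1.5 standard errors.

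**The case against.** A reader might infer that the rule biases the treatment effect toward benefit. The documents do not support that. The rule covers control as well, and effectiveness is judged against control. Bias toward benefit needs more reporting, more spread or more worsening in the video arms, and none of these is documented. More reporting in the video arms is conceivable, since they see daily videos on reducing consumption (Surveys and intervention). Control participants, however, are also contacted every day, and they too joined wanting to consume less (Participant criteria), so they might report more.

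A reader might also infer that harm would vanish, or that the rule alone creates the expected fall over time. Neither follows. A harm of +0.20 in the contrast is attenuated to +0.169 at worst in the range examined, and the promised reporting makes the cases visible. The shift over time falls short of significance even when exactly the largest 5% of increases are removed. Nor do all the worst values go: only self-reported cases are removed, and for well-being only severe ones. Reports come before t7 exists, so they cannot track the t7 change exactly, and removing exactly the largest increases is a worst case.

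It is fair to add that this is a participant safeguard, that cases may be few, and that a full protocol or analysis plan, not shown here, may define the analysis population and missing-data methods. What remains is that the article itself fixes a rule ending participation before the outcomes are measured. Reporting the instances, or a later plan, does not restore those outcomes.

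**Conclusion.** The point holds as a matter of informative missing data. Followed as written, the rule makes t7 and one-month outcomes missing because buying rose or well-being fell. Within-arm change is biased toward improvement whenever such participants are removed. Harm can be attenuated. The contrast with control can be biased in a direction and by an amount that cannot be known in advance.

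With 10% of video-arm and 5% of control participants dismissed, the bias is about −0.03 to −0.07 SD and the type I error about 6% to 13%. The sign reverses if control reports more, and the bias is about zero if reporting is equal and there is no effect. These figures rest on assumed dismissal and reporting rates, normal change scores and a baseline-post correlation of 0.6. The flaw should be fixed and is cheap to fix; it does not by itself invalidate the design.

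**What to change.** Separate the decision to stop exposure, which stays as it is, from measurement and analysis.

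1. With consent, invite dismissed participants to complete the t7 and one-month questionnaires.
2. Keep all their data and analyse them in the arm to which they were randomised.
3. Report the number of dismissals and the reasons by arm.
4. Where t7 is still missing after a dismissal, add a sensitivity analysis that assigns an unfavourable value.

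If the outcomes are obtained, the bias from this rule is removed and the sample size is unchanged. The cost is one protocol sentence, one consent line and a questionnaire link. Because the text now says dismissal from the study, the change needs the ethics committee's agreement. It should be settled before data collection, since outcomes not collected cannot be recovered.
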